### 12.2. Analysis Plans

The **primary aim** is to assess the long-term relative effect of randomization to a physical activity intervention on time until major mobility disability (defined as inability to walk 400 meters (through objective or adjudicated evidence)).

The primary study hypothesis of LIFE will be tested based on a two-tailed significance level of 0.05. In this analysis, the "intention to treat" approach will be used in

which participants are grouped according to randomization assignment.

The main comparisons of intervention groups with respect to the distribution of time until the first post-randomization occurrence of a primary outcome will be based on survival analyses. To compare intervention arms, we will use a likelihood ratio test from a Cox regression model, stratified by Field Center and gender. Failure time is measured from the time of randomization.

**Secondary aim #1** will be to assess the relative effect of randomization to the intervention on cognitive function as measured by the DSST and HVLT instruments.

Cognitive data will be collected at the baseline and 2-year visits. For the primary DSST and HVLT analysis, the data will be transformed to better approximate the conditional normality assumption if necessary. Analysis of the intervention effect will be carried out using analysis of covariance with variables in the model representing field center, gender, the baseline outcome and the intervention effect. The effect of the intervention on DSST and HVLT will be based on a two-tailed significance level of 0.05 and will use the “intent to treat” approach.

**Secondary aim #2** will be to assess the relative effect of randomization to the intervention on serious fall injuries.

The main comparisons of intervention groups with respect to the distribution of time until the first post-randomization occurrence of a serious fall injury will be based on survival analyses. To compare intervention arms, we will use a likelihood ratio test from a Cox regression model stratified by gender. Due to the expected small number of serious fall injuries, we have chosen not to stratify this outcome by field center. Failure time is measured from the time of randomization.

**Secondary aim #3** will be to assess the relative effect of randomization to the intervention on persistent mobility disability.

Of primary interest is a comparison of the probability of being classified as having major mobility disability at two consecutive assessments. This outcome will be analyzed using transitional models for categorical endpoints. A first-order Markov model will be used to compare between intervention groups the probability of being classified in the major mobility disability category at a subsequent visit, given a participant's previous classification state. Validity of the first-order versus higher-order Markov assumptions will be explored within these models.

**Secondary aim #4** will be to assess the relative effect of randomization to the intervention on the combined outcome of major mobility disability or death.

The main comparisons of intervention groups with respect to the distribution of time until the first post-randomization occurrence of the combined outcome of major mobility disability or death will be based on survival analyses. To compare intervention arms, we will use a likelihood ratio test from a Cox regression model, stratified by field center and gender. Failure time is measured from the time of randomization.

**Secondary aim #5** will be to assess the relative effect of randomization to the intervention on the proportion of 400 m walk failures over time.

This analysis will use the repeated 6-month indicators of 400 m walk status (rather than the time until the initial failure) and compare the average proportion of participants in each intervention group that fail the 400 m walk across all time points using generalized estimating equations (GEEs) that account for the dependency between repeated measures. Odds ratios for the association between 400 m walk status and intervention will be estimated after adjusting for field center, gender, a follow-up time effect, and an intervention effect. This approach is most consistent with 400 m walk serving as a marker of functional status and the trial examining whether lifestyle interventions may alter the distribution of this construct.

**Secondary aim #6** will be to assess the relative effect of randomization to the

intervention on the disability in activities of daily living.

Level of ADL disability will be repeatedly measured as a continuous, score variable. A comparison of average post-randomization levels of ADL disability between intervention groups will be performed using mixed-effects analysis of covariance techniques appropriate for repeatedly measured outcomes. These models will contain variables representing field center, gender, a follow-up time effect, the baseline level of ADL disability and an intervention effect. Initially, we will explore the appropriateness of a model containing random intercepts and slopes (for follow-up time). The appropriateness of a model containing a fixed effect for the intervention by follow-up time interaction will be evaluated.

**Secondary aim #7** will be to assess the cost-effectiveness of the intervention.

Cost-effectiveness analyses will be conducted following the guidelines of the Panel of Cost-Effectiveness in Health and Medicine. The ratio of direct costs of the physical activity intervention to the amount of quality-adjusted life years (QALYs) produced is calculated. Health care costs will be estimated and differences between the physical activity and lifestyle intervention groups will be calculated to examine whether any cost-offset may occur. LIFE takes a societal perspective. The trial uses the health education intervention as the comparator for all cost-effectiveness analyses. Results will be described as the incremental cost-effectiveness over the comparator. Sensitivity analyses will be conducted to examine whether the cost-effectiveness results change as a function of any estimates or assumptions made in the process. Decision modeling will be used to estimate long-term cost-effectiveness beyond the 1-year time horizon for which data collection is planned. Future health care costs will be discounted at a rate of 3% for any calculations or projections beyond the first year of follow-up.

**Tertiary aim #1** will be to explore the effects of the interventions on MCI/D.

Logistic regression will be used to assess whether the proportion of participants who convert to the composite outcome of MCI/D from baseline varies by intervention assignment. Baseline level of global cognitive function (3MSE score) will be used as a covariate in these analyses.

**Tertiary aim #2** will be to explore the effects of the intervention on composite measure of the cognitive assessment battery. We will also construct a composite measure to include all components of the Cognitive Assessment Battery (but not the 3MSE, which is used as to screen participants for MCI/D classification). For this composite measure of cognitive performance we will z-transform each score by dividing its difference from the baseline mean by the baseline standard deviation, and then will average the z-transformed measures. This approach, rather than adopting weighted averages, provides slightly greater emphasis on executive function.] The relative effect of the PA intervention on this composite will be assessed with analyses of covariance applied to the measures collected at Year 2, with the baseline composite included as a covariate. Differences between intervention arms for each individual test that contributes to the composite measure will be described. A similar approach will be used to assess the impact of the intervention on executive functions using a composite score for the three executive function tests (Flanker, N-back and Task Switching)

**Tertiary aim #3** will be to assess the effects of the interventions on the SPPB score and 400 m walk speed within ethnicity/race, gender and baseline physical performance subgroups. Repeated measures analysis of covariance techniques for continuous outcomes (such as described for ADLs) will be used to explore these effects (mixed effects models). Estimates of the intervention effect will be obtained within these subgroups and formal tests of interactions between intervention and subgroup variables will be performed. Forest plots will be used to graphically display the results of these subgroup analyses.

**Tertiary Aims #4** will be assessed using a Cox proportional hazards model, stratified by Field Center and gender. Failure time is measured from the time of randomization to the first sleep-wake disturbance.

**Tertiary Aim #5** will be assessed using a logistic regression model with adjustment for Field Center and gender for the outcome of dyspnea. Ventilatory capacity will be examined using two types of mixed model analysis of variance models. First, we will examine for different post-baseline mean levels of FVC and FEV1 using a model adjusting for the baseline level, time (categorical), Field Center, and gender. We will account for within-person correlation using a subject random effect. Second, we will examine for a difference in the rates of decline using a random intercept/random slope mixed model.

**Tertiary Aims #6 and 7** will be assessed using Cox proportional hazards models, stratified by Field Center and gender. Failure time is measured from the time of randomization to the occurrence of a pulmonary disorder (Aim 6) or combined cardiovascular event (Aim 7).

**Tertiary aim #8** will be to explore time by intervention interactions on the SPPB score and 400 m walk speed endpoints. Separate estimates of the intervention effect will be obtained for participants with different planned lengths of intervention. This will be achieved by introducing variables representing periods of randomization (i.e., groupings of consecutive months) into the repeated measures models for SPPB score and 400 m walking speed and exploring the interaction between these variables and the intervention effect. There may be some confounding between other factors and the month of randomization (e.g., staff familiarity with the intervention); however, this analysis could be important in determining how length of intervention may relate to efficacy. We also will use interaction terms like these to estimate intervention effects for 1-year epochs across follow-up to examine their consistency over time.

**Tertiary aim #9** will be to explore whether the relative effect of the PA intervention on measures of cognitive function varies according to baseline level of global cognitive function. Separate estimates of the intervention effect on measures of cognitive function will be obtained for participants grouped by baseline 3MS (<90 versus  $\geq 90$ ). Tests of interaction will be used to compare any differences between these groups.

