#### **4. Study Population**

The eligibility criteria for the LIFE Study identify participants who are not currently disabled but have moderate to high risk for occurrence of mobility disability and for whom the intervention is safe.

The Coordinating Center monitors the distribution of the recruited cohort with respect to age, gender, ethnicity, score on the Short Physical Performance Battery (SPPB) and other factors expected to influence the incidence rate of the trial's primary outcome. Based on this monitoring activity, targeted recruitment strategies are developed to ensure that the study cohort is racially and ethnically diverse and has a range of age and physical performance adequate to evaluate the results of this study.

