## **5. Recruitment and Retention**

### **5.1. Recruitment**

The recruitment goal of the study is to enroll 1,600 participants, approximately 200 at each of the 8 clinical sites. Participants are recruited over a 21 month period with a goal of overall minority participation of at least 22.5%. It is a recruitment goal of the Life Study that at least 45% of participants have a baseline SPPB (Short Physical Performance Battery) score of 7 or below. In order that barriers to their recruitment are minimized, this recruitment goal will not apply to ethnic minorities. All recruitment related activities are overseen by the Recruitment, Adherence and Retention Committee. The Committee coordinates press and media and assists the sites in the preparation of recruitment materials. Each clinical site develops a site-specific recruitment plan, in order to accommodate the variability across centers in catchment area characteristics, media market outlets, and access to older participants. Recruitment strategies include the use of newspaper, radio and television advertisements, direct mail, and presentations at health fairs, senior centers, medical clinics, and churches. Participants in previous studies may also be approached and ineligible participants are asked about friends who might be eligible. All recruitment materials are reviewed by the appropriate field center IRB before being used.

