#### 6.2.2. Short Physical Performance Battery (SPPB)

The SPPB, originally developed for the Established Populations for the Epidemiologic Study of the Elderly (EPESE) is a brief performance battery based on timed short distance walk, repeated chair stands and balance test (as described by Guralnik et al.) The battery is administered by trained examiners. The measurement goal for this battery is to assess lower extremity functional limitations, which indicate functional abilities and are a strong measure of risk for future disability. The test takes about 10-15 minutes to administer and can be done in the home or the clinic setting. The battery has an excellent safety record. It has been administered to over 20,000 persons in various studies and no serious injuries are known to have occurred. The components of the battery are as follows:

**Walking speed.** Walking speed is assessed by asking the participants to walk at their usual pace over a 4 m course. Participants are instructed to stand with both feet touching the starting line and to start walking after a specific verbal command. Participants are allowed to use walking aids (cane, walker, or other walking aid) if necessary, but not the assistance of another person. At the screening visit, those participants who must use a walker are excluded. Timing begins when the foot starts to move across the starting line and the time in seconds needed to complete the entire distance is recorded. The faster of two walks is used to compute walking speed.

**Chair stands.** The repeated chair stands test is performed using a straight-backed chair, which is placed with its back against a wall. Participants are first asked to stand once from a sitting position without using their arms. If they are able to perform the task, they are then asked to stand up and sit down five times, as quickly as possible. The time to complete the task is recorded.

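### The primary Cox model is valid and delivers its stated power, but leaves out baseline SPPB, which the protocol itself calls a strong risk measure

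*Protocol*

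**What the plan says.** The primary test is set out in full in Protocol sections 3.3 and 12.2: "we will use a likelihood ratio test from a Cox regression model, stratified by Field Center and gender". Section 12.2 also fixes the level: "The primary study hypothesis of LIFE will be tested based on a two-tailed significance level of 0.05". Field center and gender are the two randomization strata (section 6.4.2), and neither section names a further covariate. The model for major mobility disability or death is the same. The GEE for walk failures adjusts for center, gender and follow-up time. Appendix B sets the O'Brien-Fleming boundary on the hazard ratio from the primary Cox model.

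On SPPB, section 6.2.2 says that the battery assesses functional limitations, "which indicate functional abilities and are a strong measure of risk for future disability". Section 4 lists the SPPB score with age, gender, ethnicity and "other factors expected to influence the incidence rate" of the primary outcome. Table 10.1 schedules SPPB at the first screening visit for everyone. Entry requires a score below 10 (section 4.1.2).

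Elsewhere in section 12.2 the baseline value is a covariate: for DSST and HVLT, ADL disability, the cognitive composite, and mean FEV1 and FVC. Dyspnea has none: it "will be assessed using a logistic regression model with adjustment for Field Center and gender for the outcome of dyspnea".

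**The concern.** The protocol names SPPB as a driver of the primary outcome and measures it on every participant, but uses it in neither the randomization nor the primary analysis. Several lower-ranked outcomes are adjusted for their baseline values, while the mobility outcomes, which are the trial's main question, are not adjusted for baseline function.

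Two things are at stake. In a Cox model, adjusting for a strong predictor raises the power of the treatment test. It also removes the effect of any chance imbalance in that predictor. Planned power leaves limited room: Table 3.3.1 gives 76% at a 20% effect and 80% at 21%.

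**Working it through.** **1. The plan's own figure.** Inputs from section 3.3: N = 1600, 1:1, two-sided 0.05, control risk 18% a year rising to 21% after two years, loss 8% a year, follow-up 23 to 42 months (taken as uniform).

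Hazards: −ln(0.82) = 0.198 for years 0–2, −ln(0.79) = 0.236 afterwards, and loss −ln(0.92) = 0.083. The intervention hazards are these times the HR.

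For each arm, the event probability is the integral of hazard × event-free survival × not yet lost, averaged over follow-up. At HR 0.79 this is about 0.385 (control) and 0.320 (intervention), so events ≈ 800 × 0.385 + 800 × 0.320 = 308 + 256 = 564.

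Power = Φ(√(d/4) × |ln HR| − 1.96):
- HR 0.80, d = 567: 11.906 × 0.2231 − 1.96 = 0.697, power 75.7%
- HR 0.79, d = 564: 11.874 × 0.2357 − 1.96 = 0.839, power 80.0%
- HR 0.75, d = 554: 11.769 × 0.2877 − 1.96 = 1.426, power 92.3%

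The full row is 75.7 / 80.0 / 83.8 / 87.1 / 89.9 / 92.3%, against the printed 76 / 80 / 84 / 87 / 90 / 93%. Table A (N = 1680) reproduces equally well. The stated power therefore does not depend on covariate adjustment.

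**2. Effect of adding one prognostic covariate.** Simulation used the same rates, 16 strata, 3000 trials per setting and a Wald test (standing in for the likelihood ratio test). The covariate is one standard-normal score. Its strength is an assumption, because the protocol gives none. Control risk in year 1 was kept at 18%, and the conditional effect was calibrated so that the *unadjusted* HR stays near 0.79, the scale on which Table 3.3.1 is built.

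| Assumed prognostic HR per SD | Mean events | Unadjusted HR | Adjusted HR | Power unadjusted | Power adjusted | Gain (points) |
|---|---|---|---|---|---|---|
| 1.0 | 565 | 0.787 | 0.787 | 80.0% | 79.9% | 0 |
| 1.25 | 559 | 0.788 | 0.786 | 79.9% | 80.3% | +0.4 |
| 1.5 | 552 | 0.787 | 0.780 | 79.1% | 81.9% | +2.8 |
| 2.0 | 529 | 0.787 | 0.767 | 77.2% | 84.7% | +7.5 |

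Each power has a Monte Carlo standard error of about √(0.8 × 0.2 / 3000) = 0.7 point. Both analyses use the same simulated trials, so the differences are more precise than that, but +0.4 is still negligible.

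**3. A yardstick.** By the protocol's own tables, going from 1600 to 1680 participants raises power at a 21% effect from 80% to 82%. At a prognostic HR of 1.5 per SD, adjustment gains slightly more than those 80 extra participants.

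**4. Chance imbalance.** With about 800 per arm, the standard error of a standardized baseline difference is √(2/800) = 0.05 SD.

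**The case against.** The strongest reply is that nothing here is wrong. The test is valid, it is stratified by both randomization factors, its power was planned on a log-rank test without covariates, and that power reproduces. A separate analysis plan, which is not shown here, may add an adjusted analysis. All of this stands, and it limits the point to an improvement. It does not remove the point: the protocol fixes the test in two sections and ties the interim boundary to it, while its own text supplies the reason to adjust.

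Several stronger readings are tempting but not supported:

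- **That true power is only about 72%.** Fixing the *conditional* HR at 0.79, with SPPB below 8 at HR 2.0 and walk time at HR 1.5 per SD, gives 72.2% unadjusted and 77.0% adjusted. The 72% follows from putting 0.79 on the conditional scale. The protocol's effect sizes belong to an unadjusted test, for which power at 0.79 was 77 to 80% in the simulation.
- **That the unadjusted hazard ratio is biased toward the null.** The shift (0.787 to 0.767 at 2.0 per SD) is non-collapsibility: the two analyses estimate different quantities.
- **That the protocol calls 400 m walk time a strong predictor.** It does not. Walk performance appears as an eligibility test, the outcome test and a tertiary speed endpoint.
- **That baseline imbalance is a major threat.** A standard error of 0.05 SD does not support that.
- **That the GEE is deficient.** Section 12.2 frames it as a comparison of average proportions in the population, which can be defended without SPPB.
- **That the MCI/dementia model needs the randomization strata.** Its stated adjustment is "Baseline level of global cognitive function (3MSE score) will be used as a covariate in these analyses". Table 3.3.3 implies 27 + 10 = 37 to 40 + 24 = 64 cases. Seven center terms, gender, 3MSE and intervention make 10 parameters, or about 4 to 6 cases each. The protocol declines center stratification for serious falls because few events are expected.

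**Conclusion.** The point holds as a worthwhile, low-cost improvement to a valid primary analysis. The gain is 0 to about 7.5 points of power with the unadjusted HR held near 0.79. It rests on three assumptions: the prognostic strength of SPPB (assumed range 1.0 to 2.0 per SD), a score that behaves roughly like a normal covariate with proportional hazards, and the protocol's own event and loss rates. Because the entry limit of SPPB below 10 narrows the range, the lower part of that interval may be the realistic one.

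Dyspnea shows a smaller gap of the same kind, and only for the ATS questionnaire. That instrument is collected at SV2, whereas section 6.2.17 schedules the Borg index only at follow-up visits, so there is no baseline Borg value to adjust for.

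**What to change.** - In sections 3.3 and 12.2, pre-specify baseline SPPB score as a covariate in the Cox models, stratified by field center and gender, for major mobility disability and for major mobility disability or death. Report the unadjusted stratified hazard ratio alongside.
- In Appendix B, state before any unblinded look which of the two models drives the O'Brien-Fleming boundary. At present the boundary follows whatever the primary Cox model is.
- Optional: add SPPB to the walk-failure GEE. Baseline 400 m walk time may be a further covariate because it is baseline performance on the outcome test itself.
- In the dyspnea model, add the baseline ATS questionnaire response from SV2. Leave field center out of the MCI/dementia model.

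The cost is a few lines of text and no new data. The adjusted hazard ratio is conditional on baseline function and so is a slightly different estimand, which is why the unadjusted estimate should be shown as well.

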### 7.3. Successful Aging Program Intervention

#### 7.3.1. Contact Mode and Frequency

The successful aging program arm meets in small groups (approximately 25 participants per group), one time each week for the first 26 weeks of the intervention. From week 27 on, successful aging groups will be offered two times per month with required participation at least once per month. Telephone calls are made after missed visits to problem-solve barriers to attendance and to encourage regular participation. As undertaken in LIFE-P, those participants randomized into the Successful Aging Program will receive an individual 45 minute face to face introductory session, by a health educator, during which time the program is described and questions are answered.

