#### **10.6. Tracking Health Care Utilization and Vital Status, and HIPAA Compliance**

Health care utilization is assessed at baseline and every 6 months using a self-administered questionnaire developed at the University of California San Diego. The measure consists of 12 questions that ask about the frequency of various types of health care utilization over the previous 6 months. The questions ask about utilization of hospital days, emergency care, urgent care, primary care, telephone calls, prescriptions, and medical equipment. Health care costs are calculated by multiplying the frequency of each service by the prevailing community charge. The measure has been validated in a clinical trial of patients with chronic obstructive pulmonary disease.

In compliance with the **HIPAA** and the DHHS' Standards for Privacy of Individually Identifiable Health Information, LIFE accesses personal health information and **medical records** only after obtaining **informed consent**. Social security number, Medicare number, date of birth, and health insurance information is collected. A proxy respondent and two contact persons are also identified.

**Abstraction of hospital records.** Participants are asked to notify study personnel about any hospitalization or serious illness. At each clinic visit or telephone contact, participants are questioned about interim hospitalizations. Since any hospitalization may potentially result in changes in activity level or performance, LIFE abstracts minimal information on all hospitalizations (discharge diagnoses, procedures, and length of stay). Hospitalizations are reviewed to assess study outcomes. For fractures, type of fracture and treatment are verified by review of the medical record. Reports of **death** through regular surveillance or via databases searches are tracked by collecting death certificates and relevant medical records, including autopsy reports if available. For all medical record reviews, standard forms are completed by trained abstractors.

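### Secondary aim #7 defines its only cost-effectiveness ratio on the physical activity program's direct cost, which does not match the societal, incremental result promised in the same paragraph

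*Protocol*

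**What the plan says.** Everything at issue stands in one paragraph, Protocol section 12.2, Secondary aim #7:

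- The ratio: "The ratio of direct costs of the physical activity intervention to the amount of quality-adjusted life years (QALYs) produced is calculated".
- Health care costs: they are estimated, and "differences between the physical activity and lifestyle intervention groups will be calculated to examine whether any cost-offset may occur".
- Perspective: "LIFE takes a societal perspective".
- Comparator: "The trial uses the health education intervention as the comparator for all cost-effectiveness analyses".
- Reporting: "Results will be described as the incremental cost-effectiveness over the comparator".
- Discounting: "Future health care costs will be discounted at a rate of 3% for any calculations or projections beyond the first year" of follow-up.

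The paragraph also says that a recognized panel's cost-effectiveness guidelines will be followed, and that modeling will extend the results beyond a one-year data horizon.

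Two other sections bear on the inputs. Section 10.3.5 covers QALYs and the Quality of Well-Being scale. Section 10.6 covers utilization: "Health care costs are calculated by multiplying the frequency of each service by the prevailing community charge". Neither says how the cost components are combined into a ratio.

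**The concern.** A ratio that is incremental over a comparator has a cost difference on top and an effect difference below. Under a societal perspective, the cost difference includes health care and whatever other societal costs are counted, as well as program delivery. The only ratio defined here has the direct cost of one arm on top. No sentence subtracts what the SA program costs. The health care difference is given a separate purpose, the examination of a cost-offset, and is not assigned a place in the ratio. It is also described as a contrast with a lifestyle group, although the trial has only the PA and SA arms (sections 6.4.2 and 7.1.2).

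Cost-effectiveness is a named secondary hypothesis (section 3.1.2). Two analysts could each cite this paragraph and report different numbers: one a PA program cost per QALY, the other an incremental cost per QALY against SA. A reader who compares the result with other interventions needs to know which it is.

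**Working it through.** The protocol states no cost, QALY or cost-effectiveness figure, so there is nothing to reproduce. The check is algebra, followed by an illustration from the protocol's contact schedule.

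**1. Algebra.** Let C_PA and C_SA be program costs per participant, dH the PA minus SA difference in health care and other societal costs, and dQ the PA minus SA difference in QALYs. Assume that the QALYs produced already means dQ, the reading most favourable to the text.

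- Ratio as written: C_PA / dQ
- Incremental ratio: (C_PA − C_SA + dH) / dQ
- Written ÷ incremental = 1 / (1 − s + h), with s = C_SA/C_PA and h = dH/C_PA

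The two agree only if dH = C_SA, that is, if PA raises other costs by exactly what the SA program costs. Nothing in the protocol suggests this.

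**2. SA cost is not zero.** SA has staffed small-group sessions "one time each week for the first 26 weeks of the intervention", then sessions offered twice a month with at least one a month required. It also has an individual 45-minute introduction, calls after missed visits (section 7.3.1 and Table 7.2.2) and a monthly newsletter (section 7.4.3).

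**3. Session counts as a stand-in for program cost.** This is an assumption, because no unit costs are given. PA has two center sessions a week throughout (sections 7.2.4 and 7.2.5). Average follow-up is 2.7 years (section 14). The one-year horizon is shown as well because the Secondary aim #7 paragraph names it, although Table 10.1 schedules the quality-of-life and utilization forms through month 42 and at the post-intervention visit.

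*2.7 years* = 2.7 × 365.25/7 = 140.9 weeks.
- PA: 2 × 140.9 = 281.8 sessions
- Time after week 26: 114.9 weeks, about 26.4 months
- SA: 26 + 26.4 = 52.4 (monthly) to 26 + 2 × 26.4 = 78.8 (twice monthly)
- s = 52.4/281.8 = 0.186 to 78.8/281.8 = 0.280

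*One year* = 52 weeks, with 6 months after week 26.
- PA: 2 × 52 = 104 sessions
- SA: 26 + 6 = 32 to 26 + 12 = 38
- s = 32/104 = 0.308 to 38/104 = 0.365

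**4. Factor by which the written ratio exceeds the incremental one when h = 0**, 1/(1 − s):

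| Horizon | SA monthly | SA twice monthly |
|---|---|---|
| 2.7 years | 1/0.814 = 1.23 | 1/0.720 = 1.39 |
| One year | 1/0.692 = 1.44 | 1/0.635 = 1.58 |

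If an SA session costs k times a PA session, s becomes k·s. The factor moves toward 1 for small k and upward for large k.

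**5. Effect of the health care term.** Over 2.7 years, let h run from −0.30 to +0.30 (assumed).

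- Lowest: s = 0.186, h = +0.30 gives 1/1.114 = 0.90
- Highest: s = 0.280, h = −0.30 gives 1/0.420 = 2.38

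The range includes 1, so the net direction is not determined.

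**The case against.** The strongest reply is that one sentence is being read apart from its neighbours. The paragraph fixes the comparator for all cost-effectiveness analyses, promises incremental results, computes between-arm health care differences and adopts external guidelines. An offset is by nature something set against program cost, so the ratio sentence may be loose shorthand. This shows incremental intent, and that part stands. It does not remove the conflict, because the only ratio actually defined is a different quantity from the one intended.

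Three stronger readings are tempting, and the protocol does not support them:

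- *A cost-offset can never enter the ratio.* The text does not exclude this; it is silent on how the offset is combined.
- *Projected QALYs and program costs go undiscounted.* The text names only health care costs for the 3% rate. Silence on the rest is not a rule against discounting it. The adopted guidelines, or an analysis plan that is not shown, may settle it.
- *The written ratio is biased against PA.* Omitting SA cost does push the ratio up, but the health care term has unknown sign and can reverse this.

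The objection that sessions are a weak proxy for cost also stands. SA groups have about 25 people, while PA group size is not stated. PA sessions involve 40 to 60 minutes of instruction and use equipment. The factors are illustrations, not estimates from the plan. Finally, the contrast with a lifestyle group is most likely a naming slip.

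**Conclusion.** The point holds as an internal inconsistency. The ratio defined in Secondary aim #7 is a PA program cost per QALY, while the same paragraph promises a societal, incremental result over health education. As written, SA program cost is missing from the numerator and the health care difference has no stated place in it.

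The true size and net direction cannot be derived from the protocol. If cost is proportional to center sessions, health care costs are equal and the QALY denominator is the same, leaving out SA cost inflates the ratio by 1.23 to 1.39 over 2.7 years and by 1.44 to 1.58 over one year. With an assumed health care difference of up to 30% of PA program cost in either direction, the 2.7-year factor runs from 0.90 to 2.38.

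The discounting wording is a secondary matter of clarity. The issue is confined to a secondary economic aim and does not touch the primary test. It should be corrected because the protocol's only formula for a named hypothesis contradicts its own description of the result.

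**What to change.** In section 12.2, Secondary aim #7:

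1. Define the primary ratio as [(PA program cost − SA program cost) + (PA − SA difference in health care and any other societal costs counted)] ÷ (PA QALYs − SA QALYs). Since the perspective is societal, list which costs beyond health care are counted, or say that none are.
2. Keep direct PA cost per QALY, if wanted, only as a labelled descriptive figure.
3. In the health care cost sentence, replace the lifestyle group with the successful aging group.
4. As a clarification, state that the 3% rate applies to all costs and to QALYs beyond year 1.

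The cost is a short text amendment plus the work of costing SA delivery. Intervention contacts are already recorded (section 7.4.1), and utilization and quality-of-life data are scheduled for all participants (sections 6.2.13 and 6.2.14, Table 10.1). Items 1 to 4 need no new participant data unless other societal costs are counted that these forms do not capture.
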